### Data Analysis

Descriptive statistics will be used to describe relevant demographic data, such as the frequency and the percentage for the categorical data as well as the mean and the SD for the outcome measurements. There will be three analysis plans to prove the non-inferiority of the application, which are (1) repeated-measures ANOVAs (Goodman et al., 2016; Twisk et al., 2018), which will be used to test for differences between the TAU and the intervention groups (i.e., between-subjects factor) in the treatment at the four time points (i.e., within-subjects factor). We would like to assess whether the outcomes will be improved after treatment using the application and the TAU. An analysis will be conducted to check the constancy assumption. Then, both (2) the intention-to-treat (ITT) and (3) the per-protocol analysis will be performed. Previous studies showed that performing both analyses will produce more convincing results to conclude the non-inferiority of a new treatment (Hahn, 2012; Walker, 2019). The ITT analyses will be chosen to handle the missing value due to the protocol deviations, withdrawal, and non-compliance (Gupta, 2011) whereas the per-protocol analysis will minimize the factors that would make the two groups seem similar (Walker, 2019).

The statistical hypotheses in this non-inferiority trial use Δ. The null hypothesis states that the intervention using the application will be inferior to the TAU (H0: TAU–SAENA ≥ Δ). The alternative hypothesis states that the intervention will not be inferior (will have a similar effect) to the TAU although the effect may not be as good as the TAU within the extent of margin (H1: TAU–SAENA < Δ). Of note, 95% CI will be used. The interval will be the mean difference between the outcome measures of the two groups. The formula is as follows:

$$\begin{array}{l} \left(\mu_{saena}-\;\mu_{TAU}\right)\pm 1.96\sqrt{\frac{\sigma_{saena}^{2}}{n_{saena}}+\frac{\sigma_{TAU}^{2}}{n_{TAU}}} \end{array}$$

μ, mean; Tau, standard deviation; *n*, sample.

The 1.96 is the *z*-value, and the value from this formula can now be compared with Δ. If the interval remains above Δ, then the inferiority of the application will be proven according to the standards that have been set. In contrast, if the upper limit for treatment difference by the intervention group compared to the TAU group is < Δ, then the non-inferiority will be concluded.

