According to several studies, online counseling is needed by students because they cannot access mental healthcare (Chan, 2020; Li and Leung, 2020; Novella et al., 2020). Although there are several limitations, the studies showed that online counseling is effective in dealing with psychological issues such as emotional distress, anxiety, and social withdrawal symptoms. The study aimed to test whether or not the mobile-based counseling application called “SAENA” can help the students increase their (1) CSE and (2) resiliency, as well as decrease their (3) level of depression. Therefore, the hypothesis is that the application is equivalent to the Treatment-As-Usual (TAU) in increasing the personal resources of students.

The quality of a study depends on how well-both the design and execution phases of the project are (Ott, 1991). By writing the protocol, a gap between these phases could be examined carefully and fairly. The protocol also helps the researchers in providing study documentation as well as in increasing the efficiency of the projects (Ott, 1991). Therefore, this study will explain the protocol of the non-inferiority trial of the mobile-based counseling application.

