### Participants

The target population in the study will be University students who have academic-related psychological problems. The inclusion criteria of the sample are a University student, aged 18–25 years old, having academic-related problem(s), and registering as a participant in this study. The academic-related problems that will be included in the study are (1) (educational) adjustment difficulties; (2) difficulties in writing a thesis; (3) academic procrastination; (4) poor self-regulation for learning; and (5) a low grade point average (GPA). The study will exclude students with (1) physical disabilities; (2) under the care of mental health professionals; and (3) the score of PHQ-9 more than 14 (having severe depression), (Rahmadiana et al., 2019).

The participants of the study will be those who register in a University counseling center. They will be then screened with the PHQ-9. If they are willing to participate in the study, the research assistants will give informed consent and the right to withdraw from the study at any given time they wish to. The students who decline to join the study or withdraw from the study will be followed up to identify their reasons for declining and withdrawing from the study. The students have a right to undergo post-trial treatment if needed.

The sample size is a sensitive issue in the non-inferiority trial (Hahn, 2012). Large sample size is usually needed. However, if the new intervention is assumed to be slightly more effective than the TAU, the number of samples can be reduced. The mobile-based counseling application can be assumed to be more practical for the students in this country. Those who live remotely can still access the psychological services. The data from the University counseling center in 2020 were also a source of consideration in determining the sample size. The center admitted 482 clients in that year, with an average of 40 clients per month. With 80% CI, the expected SD will be one, and the inferiority margin (Δ) will be 0.24. It was calculated that the number of participants per arm needs to be 215 and the total sample size needs to be 430.

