### Determining an Inferiority Margin of the Trial

In the non-inferiority trial, the researchers need to determine Δ (Hahn, 2012). In this study, the margin is the maximum acceptable extent of non-inferiority of the mobile-based counseling application. The maximum limit of Δ can be set to the entire effect size of the active control treatment (Hahn, 2012). Several proposals for choosing the inferiority margins in the context of SFBT have been made (Table 1). There are several suggestions for the maximum difference in outcomes that will be considered clinically irrelevant. It ranges from *d* = 0.17 to *d* = 1.76. The smallest margin was suggested by Schmit et al. (2016), (*d* = 0.24) for the treatment of internalizing disorders. Thus, in this study, it was decided to use the inferior margin of 0.22 (i.e., the inferior margin up to 0.22), corresponding to a small effect size.

**Table 1 T1:** The effect size from the solution-focused brief therapy (SFBT)-related studies.

**Previous studies**	**Effect size**
Impacts on academic and emotional difficulties (Daki and Savage, 2010)	≈0.13 (partial eta squared, medium effect size)
Meta-analysis of solution-focused brief therapy for treating symptoms of internalizing disorders (Schmit et al., 2016)	≈0.24 (Hedges' g, small effect size)
Examining the effectiveness of solution-focused brief therapy: a meta-analysis (Kim, 2008)	0.26–0.38 (Cohen's *d*, small effect size)
SFBT for health-related psychosocial outcomes (Zhang et al., 2018)	0.34 (Cohen's *d*, small effect size)
Solution-focused brief therapy in schools: A review of the outcome literature (Kim and Franklin, 2009)	0.38–1.76 (Cohen's *d*, medium to large effect size)

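### An ANOVA that tests for a difference is listed as proof of non-inferiority beside an interval-versus-margin rule, and ITT is named as the way missing values are handled

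*Protocol article*

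**What the plan says.** In the protocol article, Data Analysis opens the inferential plan with: "There will be three analysis plans to prove the non-inferiority of the application, which are (1) repeated-measures ANOVAs". These ANOVAs are the analyses "which will be used to test for differences between the TAU and the intervention groups", over four time points. The section gives them a second purpose as well, to see whether outcomes improve under either treatment. The second and third items are the ITT and per-protocol analyses. On missing data it says: "The ITT analyses will be chosen to handle the missing value due to the protocol deviations, withdrawal, and non-compliance".

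The section then sets margin-based hypotheses (null: TAU minus SAENA is at least Δ; alternative: it is below Δ). It adds "Of note, 95% CI will be used" and prints an unadjusted interval for SAENA minus TAU with multiplier 1.96. Non-inferiority is concluded if the upper limit is below Δ. How this rule ranks against the ANOVA is not stated.

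Outcome Measurements gives the intervention arm five assessments (T0 to T4). Control students have three to five, depending on how many sessions they attend, and the last falls three months after their own final session. The Introduction says "the hypothesis is that the application is equivalent to the Treatment-As-Usual (TAU", and the Abstract and Discussion also speak of equivalence.

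**The concern.** A test for a difference asks whether the arms differ at all. A non-significant result may only mean that the data are too few or too noisy, and a significant one can occur when the application is worse by a clinically trivial amount. Neither result answers the non-inferiority question. When such a test stands first among the proofs, next to a margin rule and with no order of precedence, a discordant result can be settled after the data are seen.

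The ITT sentence raises a related problem. ITT defines who is analysed and in which arm; it does not supply an outcome for a student who has none. The article relies on ITT and per-protocol together to make the conclusion convincing, and that support is weaker if the handling of missing outcomes is left to a label.

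Finally, a one-sided alternative can support non-inferiority but not equivalence, so the stated aim goes beyond what the test can show.

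**Working it through.** **Inputs.** Participants section: "the number of participants per arm needs to be 215 and the total sample size needs to be 430", and "With 80% CI, the expected SD will be one, and the inferiority margin (Δ) will be 0.24". Determining an Inferiority Margin section: "it was decided to use the inferior margin of 0.22". Data Analysis: 95% interval, multiplier 1.96. The true difference used for sizing is not given; 0 is assumed. The documents give no baseline-to-outcome correlation ρ and no dropout rate.

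**1. The plan's own figure.** n per arm = 2(z₁₋α + z_power)²/Δ², with SD 1.
- Δ = 0.24, one-sided 0.05, 80% power: 2(1.645 + 0.842)²/0.0576 = 214.7, so 215. This reproduces the article exactly, provided the 80% is read as power.
- The 1.96 interval corresponds to one-sided 0.025. That needs 273 per arm at Δ = 0.24 or 325 at Δ = 0.22.

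**2. The ANOVA as proof.** SE = √(2/215) = 0.0964. If the application is truly worse by Δ, the chance that a two-sided 5% test at a single time point is non-significant is about Φ(1.96 − Δ/SE).
- Δ = 0.22: Φ(1.96 − 2.281) = Φ(−0.321) = 0.374.
- Δ = 0.24: Φ(1.96 − 2.488) = Φ(−0.528) = 0.299.

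A correct margin test at the same truth passes 2.5% of the time.

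**3. Time points.** The ANOVA has four levels of time. The intervention arm has five assessments. A control student with one session has three (T0, T1, TX). Even if the four are taken as T0–T3 or T1–T4, many controls may lack some of them, and the control follow-up is dated from a different event for each person. Classical repeated-measures ANOVA needs the same complete grid for everyone.

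**4. Power with and without baseline.** Unadjusted power is Φ(Δ/SE − 1.96). Adjustment multiplies SE by √(1 − ρ²). This is an ANCOVA approximation at one time point, with no dropout and a true difference of 0.

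| ρ (assumed) | Δ = 0.24 | Δ = 0.22 |
|---|---|---|
| none (unadjusted) | 70% | 63% |
| 0.3 | 74% | 67% |
| 0.5 | 82% | 75% |
| 0.6 | 88% | 81% |

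Reaching 80% requires 1 − ρ² ≤ 215Δ²/[2(1.96 + 0.842)²]. This gives ρ ≥ 0.46 at Δ = 0.24 and ρ ≥ 0.58 at Δ = 0.22.

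**5. Sign of the rule.** The hypotheses use TAU minus SAENA, while the printed interval uses SAENA minus TAU. Applied to the printed interval, with higher CSE better, an upper limit below Δ would be met by an application worse by Δ with probability Φ(2Δ/SE − 1.96). At Δ = 0.22 that is Φ(2.60), over 99%. The direction must be settled before the margin rule can carry the conclusion alone.

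**The case against.** The strongest reply is that Data Analysis already contains margin-based hypotheses and an interval-versus-Δ rule, and that this is the only explicit decision rule in the article. That is correct. A reader might infer that the trial will declare non-inferiority from a non-significant ANOVA, or that its false-positive rate is 37%. The article says neither. The 37% and 30% belong to a rule it does not state, and they are computed for a single-time test rather than a four-point ANOVA. What remains is the role the article assigns to the ANOVA: a proof of non-inferiority, with no ranking against the margin rule.

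A reader might also infer that both the ITT and per-protocol results will be completer analyses. The two-mean formula can use only observed or filled-in values, but imputation may be specified in a document that is not shown, so silence here does not establish a completer analysis. The statement that ITT handles missing values is still wrong as written.

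Third, an unadjusted interval is valid in a randomised trial, and covariate adjustment is commonly left to the analysis plan. This is accepted: the lack of a baseline term is not an error.

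Fourth, the design and hypotheses are plainly non-inferiority, so the equivalence language may be loose usage. It is a wording correction, but it affects the stated hypothesis.

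**Conclusion.** The point holds for the stated role of the ANOVA, its mismatch with the assessment schedule, the description of ITT, and the equivalence wording. The 37% and 30% pass rates show what is at stake if non-significance is read as proof. They assume SD 1, 215 analysed per arm and one time point.

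Baseline adjustment is a worthwhile addition because, at 215 per arm, the planned 1.96 interval has only 70% or 63% power. It recovers some of that loss, and the amount depends wholly on ρ, which is assumed here. At ρ = 0.3 power stays below 80% for both margins.

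It would be tempting to conclude that a mixed model cures everything at once. It does not. A mixed model used to test for a difference proves no more than the ANOVA. It needs a common time point that the article does not fix, it deals with missing outcomes only under missing at random, and it leaves the 0.22/0.24 margin conflict and the sign conflict open.

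Randomization places allocation before the initial assessment. The article does not say when students learn their arm, so it cannot be concluded that baseline scores are affected, but the order matters if baseline becomes a covariate.

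**What to change.** - Make the comparison of the 95% interval with the margin the only basis for the non-inferiority conclusion. Use one margin and one direction of difference throughout. Keep the ANOVA, if at all, to describe change over time.
- Name one time point common to both arms. Estimate SAENA minus TAU and its 95% interval there from a baseline-adjusted model, for example a mixed model, using all available data from all randomised students as allocated. Repeat it in the per-protocol set.
- Replace the ITT sentence: ITT defines the analysis set, and the model handles missing outcomes under missing at random. Add a sensitivity analysis that gives missing SAENA outcomes less favourable values.
- Have baseline completed before students learn their arm, or record this as a limitation.
- Replace equivalence with non-inferiority in the Abstract, Introduction and Discussion.

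The cost is wording and modest analyst time, plus reliance on missing at random for the main estimate. The model itself needs no new outcome measure. Fixing a common time point may mean aligning the timing of one control-arm assessment, because the current follow-up is counted from each student's own last session.

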## Materials and Methods

### Study Design

This study describes a study that will be conducted as a two-armed parallel randomized controlled non-inferiority trial. The trial is in line with the guidelines for the protocol content of the non-inferiority trial (Piaggio et al., 2012). It will also be based on the guidance of the Standard Protocol Items: Recommendations for Intervention Trials (SPIRIT) Statement (Tetzlaff et al., 2012; Chan et al., 2013). The non-inferiority scheme will be used in this study because the application is not aimed to be more powerful or effective than the usual treatment but aimed to increase the practicality of the counselors to store the data in the application and to hide personal contacts (e.g., email addresses or online meeting IDs) by solely using the application only for the counseling purposes (Hahn, 2012).

To eliminate the assay sensitivity, bias, and constancy assumption (ABC) of this non-inferiority trial, there are several things included in the design. First, the outcome measurement tools that will be used in both groups are reliable. Second, besides using randomizing in allocation and double-blinding procedure, the control group will get the TAU without any intervention to prevent a bias. Third, the data will be collected in the same period for both groups to minimize any situational effects, such as the COVID-19 pandemic-related government policies in this country (Walker, 2019).

The proposed study will be a parallel group design comparing two types of treatments. The intervention group will use the application whereas the control group will get the TAU. The intervention group will have three counseling sessions for a month; meanwhile, the control group will have many sessions based on the need of each individual. All outcomes will be assessed repeatedly using online self-reported forms, which will be facilitated by research assistants. The assessments will be taken (1) before the intervention, (2) after each session (a session/week), and (3) after 3 months. The study design is shown in Figure 1.

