### Outcome Measurements

The participants in the intervention group will complete the assessments at (1) the baseline (T0); (2) at the end of the first counseling session (T1); (3) at the end of the second counseling session (T2); (4) at the end of the third counseling session (T3); and (5) 3 months after the third counseling session (T4). There will be a week interval between the counseling sessions (T1, T2, and T3). Meanwhile, the participants in the control group will be measured at 3–5 points in time depends on the number of counseling sessions they have. They will fill the questionnaires at (1) the baseline (T0); (2) at the end of their counseling session(s), (T1 and/or T2 and/or T3, etc.); and (3) 3 months after the last session (TX). The data will be collected using the online forms and will be assisted by the research assistants.

The primary outcome of the proposed study will be CSE measured by the Coping Self-Efficacy (CSE) Scale. The Indonesian version of the CSE consists of 26 items with 11-point scale (0–10). The scale has good reliability (*r* = 0.92), (Nurhidayah, 2020). The total score will be used as an indicator of the level of CSE of participants. The CSE is defined as a belief about own ability of an individual to perform specific coping behavior (Chesney et al., 2006). Self-efficacy serves as evidence in measuring changes in the coping ability of individuals, especially for those who seek professionals to solve their problems (Chesney et al., 2006; Yoo et al., 2020).

The secondary outcomes of this study will be (1) resilience and (2) level of depression. Resilience is defined as the capacity of a dynamic system to adapt successfully to adversity that threatens system function (Masten, 2014). The Resilience Scale (RS-14), (Surzykiewicz et al., 2019), which will be used to measure this variable, has five dimensions, namely, equanimity, perseverance, self-reliance, meaningfulness, and existential aloneness. The short version of the RS test has been adapted to the Indonesian language. It has 14 items with a 7-point Likert scale (*r* = 0.87). The scale has good Construct Validity Fitness Indexes [Non Normed Fit Index (NNFI) = 0.99, Root Mean Square Error of Approximation (RMSEA) = 0.027, and Standardized Root Mean Residual (SRMR) = 0.026], (Valentino, 2021).

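### The repeated-measures analysis fixes four time points where five are scheduled in the application arm and three to five in the control arm, and the non-inferiority interval on coping self-efficacy names no visit

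*Protocol article*

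**What the plan says.** Three parts of the protocol article bear on this point.

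- **Schedule.** Study Design states: "The assessments will be taken (1) before the intervention, (2) after each session (a session/week), and (3) after 3 months". With three sessions in the application arm, that is five assessments. Outcome Measurements lists them as T0, T1, T2, T3 and a last one "3 months after the third counseling session (T4". For the control arm it says that "the participants in the control group will be measured at 3–5 points in time depends on the number of counseling sessions they have", the last being "3 months after the last session (TX".
- **Repeated-measures analysis.** Data Analysis lists repeated-measures ANOVA first among three analyses meant to show non-inferiority. It compares the arms "in the treatment at the four time points (i.e., within-subjects factor". The four are not named.
- **Decision rule.** The primary outcome is the CSE total score, with no primary visit. On the interval, Data Analysis says: "The interval will be the mean difference between the outcome measures of the two groups". The formula has one mean, one variance and one sample size per arm, and no index for time. It does not say whether the means are scores at a visit, changes from baseline or averages.

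**The concern.** The visit count in the analysis contradicts the article's own schedule, and the rule that decides the trial cannot be applied to repeated measurements as written. Someone must still choose the visit, and nothing in the article prevents that choice from being made once the data are seen.

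Two things are at stake. First, if the four time points are T0–T3, the 3-month outcome is collected but never enters this analysis; if they are T1–T4, baseline is left out. Second, the choice matters more in a non-inferiority trial than in a superiority trial. Randomised arms are expected to be equal at T0, and T1 follows a single session. Any contrast that mixes such scores with later ones moves towards zero if a deficit builds up over the course, and movement towards zero favours the claim.

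**Working it through.** **Step 1: count the assessments.**

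- Application arm: 1 baseline + 3 post-session + 1 follow-up = 5.
- Control arm: 3 to 5. Taking away T0 and TX leaves 1 to 3 post-session assessments.
- Data Analysis: 4.

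No application participant has four scheduled assessments. A control participant has four only with two sessions, and these are then T0, T1, T2 and TX, which is neither T0–T3 nor T1–T4. A control participant with fewer than three sessions has no T3.

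**Step 2: reproduce the plan's sample size.** For a two-group comparison of means with SD 1, margin 0.24, true difference 0 and 80% power, a one-sided level of 0.05 gives

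n = 2(1.645 + 0.842)² / 0.24² ≈ 215 per arm,

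which matches. The one-sided level is inferred, and the article's 80% (labelled a confidence level) is read as power. The formula is for one comparison at one time, so naming a single visit does not change it.

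**Step 3: show what the open choice could do.** This is an illustration. The inputs from the article are 215 per arm, margin 0.24, SD 1 and z = 1.96. Assumptions not in the article are:

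- the contrast is a simple average of k visits;
- the SD is 1 at every visit, and the margin stays in single-visit SD units;
- the between-visit correlation ρ is 0.5 to 1.0;
- the true deficit of the application is 0, 0.08, 0.16, 0.24, 0.24 at T0–T4.

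Formulas: v = (1 + (k − 1)ρ)/k; SE = √(2v/215); P(claim) = Φ((0.24 − mean deficit)/SE − 1.96).

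| Contrast | Mean deficit | P(claim), ρ = 0.5 | P(claim), ρ = 1.0 |
|---|---|---|---|
| T3 or T4 alone | 0.24 | 0.025 | 0.025 |
| Average T1–T4 | 0.18 | 0.120 | 0.090 |
| Average T0–T4 | 0.144 | 0.250 | 0.167 |
| Average T0–T3 | 0.12 | 0.350 | 0.237 |

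Worked example for T0–T3, ρ = 0.5: v = 2.5/4 = 0.625; SE = √(1.25/215) = 0.0762; 0.12/0.0762 − 1.96 = −0.39; Φ = 0.35.

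**Step 4: vary the assumptions.**

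- Margin 0.22, which the article also states, with the deficit rising to 0.22: 8–11% (T1–T4), 15–22% (T0–T4), 21–30% (T0–T3).
- Full deficit of 0.24 already at T1: 9–12% (T0–T3) and 7–9% (T0–T4). The T1–T4 average then has mean deficit 0.24, so its rate does not exceed 2.5%.
- Deficit of 0.24 appearing only at T4, with T0–T3 averaged: mean deficit 0, rate 70–88%.

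**The case against.** The strongest objection is that the averaging is not in the article. The ANOVA is one of three listed analyses. The decision rule is set out separately as a plain two-sample interval, and the sample size corresponds to one comparison at one time. A reader might infer that the non-inferiority decision rests on the ANOVA's between-arm term, baseline included, and that the trial therefore has a false-claim rate of a quarter or a third. The text does not support this. It never feeds the ANOVA contrast into the interval, and T0 belongs to the average only under some readings of the four time points. Under T1–T4, baseline is out and the 3-month visit is kept. A reader might likewise infer that the 3-month outcome is certainly dropped; that too holds only under some readings.

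The figures also depend on the scale. If the averaged score is standardised by its own SD, then at ρ = 0.6 the rates are about 17% (T0–T3), 10% (T0–T4) and 4% (T1–T4), against 32%, 23% and 11% with the margin in single-visit SD units.

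Finally, this is a journal article, its design figure is not shown, and finer definition of a contrast is commonly left to a full protocol or analysis plan. That is fair for the choice between change score and visit-specific estimate. It does not cover a stated count that the article's own schedule contradicts, or a fully written pass/fail rule that lacks the visit it needs.

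**Conclusion.** The point holds in two parts that rest on the text alone. The four time points do not match the five assessments of the application arm or the three to five of the control arm, and the interval that decides non-inferiority on the CSE total is tied to no visit.

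Dilution is a possible consequence, not a stated feature of the plan. Under the linear profile, with the margin at 0.24 and correlation 0.5–1.0, it would raise the false-claim rate from 2.5% to about 9–12%, 17–25% or 24–35%, depending on which visits are averaged. Other assumed profiles, margins or scalings give lower or higher values. If a single late visit was intended, there is no dilution, but the article does not let a reader know that.

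**What to change.** In Data Analysis:

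1. Reconcile the number of time points with Outcome Measurements for both arms. Replacing four with five is not enough, because control participants have three to five assessments and five levels cannot be a common within-subjects factor.
2. State that non-inferiority is decided on the CSE total at one post-treatment visit named in advance and present in both arms. The 3-month follow-up (T4/TX) is one such visit, as it is defined from the last session in each arm. T3 is not, because controls with fewer than three sessions do not have it.
3. Use T0 as a baseline covariate and not as an outcome level. Use the per-session assessments only to describe the course of change.

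The article does not rank the 3-month visit above the end of treatment, so the choice is the investigators'. What matters is that it is fixed before outcome data are seen.

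The cost is a few sentences. No new data are needed and the sample-size formula is unchanged. A single-visit contrast is slightly less precise than an average over visits.

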### The Mobile-Based Counseling Application: SAENA

The application was developed in four major steps as follows: First, the application and a counseling protocol were developed. The application facilitates the helping relationship between the students and the counselors through written texts, voice calls, and video calls. These three communication modes can be used interchangeably during counseling sessions. The counseling protocol was developed based on the solution-focused brief therapy (SFBT) approach (Bavelas et al., 2013). The approach is effective in a lot of contexts (Kim, 2008; González Suitt et al., 2016), except for complex psychological problems (Chaudhry and Li, 2011). As a result, in the study, the participants will be screened using the Patient Health Questionnaire (PHQ-9) to exclude those with severe depressions. Second, the professionals who will perform the counseling were trained in using the application. However, the counselors need to have a prior experience in conducting micro-skills in a face-to-face counseling context. Third, a feasibility study was conducted. Based on this study, several improvements were made in the application and the protocol. Finally, the protocol of the non-inferiority trial was developed.

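### The printed non-inferiority interval treats students as independent although counsellors deliver the sessions; the direction and size of the error depend on staffing that the article does not state

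*Protocol article*

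**What the plan says.** The Data Analysis section defines the decision interval. It states that "Of note, 95% CI will be used" and that "The interval will be the mean difference between the outcome measures of the two groups". It then prints the difference in means ± 1.96 times the square root of the sum of each arm's variance divided by its number of participants, and adds that "the value from this formula can now be compared with Δ". The other model described there, a repeated-measures ANOVA, has arm as the between-subjects factor and time as the within-subjects factor. Neither has a counsellor term.

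On delivery, the section on the SAENA application says that "the professionals who will perform the counseling were trained in using the application" and describes the application as the channel between students and counsellors. Study Design and Outcome Measurements give control students counselling sessions too, as many as each needs. The Participants section recruits from a university counselling centre and concludes that "the number of participants per arm needs to be 215 and the total sample size needs to be 430". Under Randomization, individual students are allocated by registration number, with no mention of counsellor.

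**The concern.** The printed standard error is correct only if outcomes within an arm are independent. When one counsellor treats several students, those students share that counsellor's skill and style, and their outcomes may be correlated. Non-inferiority is decided by whether one confidence limit clears Δ, so a wrong standard error acts directly on the conclusion. If the interval is too narrow, the application is declared non-inferior too often. If it is too wide, some precision is thrown away.

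The article prints this formula as the decision rule, so this is a stated choice and not a detail left to a fuller document.

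**Working it through.** **Inputs from the article.** 215 students per arm. SD 1 ("With 80% CI, the expected SD will be one"). In the Participants section, "the inferiority margin (Δ) will be 0.24"; in the margin section, "it was decided to use the inferior margin of 0.22". The analysis uses a two-sided 95% interval, so the nominal one-sided error is 2.5%.

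**Inputs not in the article, therefore assumed.** Students per counsellor (m), ICC, and whether counsellors work in one arm or both.

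**The plan's own sample size.** With margin 0.24, SD 1, true difference 0, one-sided alpha 0.05 and 80% power (reading the article's 80% as power), n = 2 × (1.645 + 0.842)² / 0.24² = 214.7, rounded up to 215 per arm. This reproduces the stated figure with independent students, so it contains no design effect.

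**The printed interval.** SE = √(2/215) = 0.0964. Half-width = 1.96 × 0.0964 = 0.189 SD.

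**Case A: counsellors nested in arm.** The variance is multiplied by the design effect DE = 1 + (m − 1) × ICC. The half-width should be 0.189 × √DE. The actual one-sided error of the printed rule at the margin is Φ(−1.96/√DE).

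| Assumption | DE | Half-width (z = 1.96) | One-sided error |
|---|---|---|---|
| m = 10, ICC 0.01 | 1.09 | 0.197 | 3.0% |
| m = 20, ICC 0.05 | 1.95 | 0.264 | 8.0% |
| m = 5 (43 counsellors per arm), ICC 0.01 | 1.04 | 0.193 | 2.7% |
| m = 43 (5 counsellors per arm), ICC 0.10 | 5.20 | 0.431 | 19.5% |

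The first two rows are the working range; the last two show how far the result moves under other assumptions. A simulation of the printed rule with 5 counsellors per arm, with the true difference set at the margin, gave errors of 7.5% (ICC 0.02) and 13.5% (ICC 0.05), against 7.4% and 13.3% from the formula.

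These half-widths are lower bounds because they use z. With m = 20 there are 215/20 ≈ 11 counsellors per arm, hence roughly 11 + 11 − 2 = 20 degrees of freedom. The t-value of 2.086 then gives 2.086 × 0.0964 × √1.95 ≈ 0.28.

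The half-width reaches 0.22 at DE = (0.22/0.189)² ≈ 1.35 and 0.24 at DE = (0.24/0.189)² ≈ 1.61. Beyond those points a valid interval could not show non-inferiority at an observed difference of zero, while the printed one would.

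**Case B: the same counsellors serve both arms evenly, with no counsellor-by-arm interaction.** The counsellor effect cancels from the difference, so the variance is multiplied by 1 − ICC. For ICC 0.01 to 0.10 the factor is 0.99 to 0.90, the half-width should be 0.188 to 0.179, and the error of the printed rule is 2.4% down to 1.9%. Simulation with 5 counsellors gave 2.4% (ICC 0.02) and 2.25% (ICC 0.05).

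**Power at margin 0.24 with a 95% CI and n = 215 per arm.** Power = Φ(0.24/(0.0964 × √DE) − 1.96).

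- DE 1 (independent students): about 70%
- DE 1.09: about 66%
- DE 1.95: about 43%

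The 70% starting point is below 80% because the sample size matches one-sided 0.05 while the analysis uses a 95% interval. That is a separate matter from clustering.

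**The case against.** A reader might infer that the interval is probably too narrow. The article does not support that. It requires counsellors nested in arm, or a counsellor-by-arm interaction, together with a non-zero ICC, and none of these is stated. Recruitment is through a university counselling centre, and application counsellors must already have face-to-face experience, so the same staff serving both arms is quite compatible with the text. With balanced crossing and no interaction, the printed interval is slightly conservative. This objection stands: the article fixes neither the sign nor the size of the error.

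It is also true that no section says each counsellor sees several students, or who delivers usual treatment. Several students per counsellor is an inference: for 430 clients of a counselling centre to be free of clustering, almost every student would need a different counsellor. The inference is reasonable but should be labelled as one.

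The last objection is that a condensed article commonly leaves therapist effects to the full protocol or analysis plan, and that the expression is the textbook interval for a difference in means. This stands for counsellor numbers and caseload, whose absence is no fault. It does not stand for the formula, which is printed and named as the quantity to compare with Δ.

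**Conclusion.** The point holds in a conditional form. The decision interval, the ANOVA and the sample size all treat students as independent, which does not fit counselling delivered by professionals to about 430 students.

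If counsellors are nested in arm, the interval is too narrow and false claims of non-inferiority become more frequent, by an amount that ranges from minor to serious within the assumed range. If they are evenly crossed without interaction, the interval is slightly too wide and the cost is a little lost precision. The two risks are unequal, and the Randomization section describes no allocation by counsellor that would secure an even crossing. All figures rest on the assumed caseload, ICC and staffing pattern, together with the article's SD of 1 and 215 students per arm.

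**What to change.** - Add a counsellor ID for each student to the data management form. Without it, the problem may not be repairable after data collection.
- State how many counsellors there are and whether they work in one arm or both.
- Take the SAENA − TAU difference and its 95% CI from a linear mixed model with a counsellor random effect: arm-specific if counsellors are nested; counsellor plus counsellor-by-arm if they are crossed. Use small-sample degrees of freedom.
- Keep the printed formula as a sensitivity analysis.
- If counsellors are nested, state the design effect and its consequence for the sample size.

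The cost is one extra data field and a different model. If counsellors are nested, the valid interval is wider and the power loss is not always small: at margin 0.24 it is about 4 percentage points at design effect 1.09 (70% to 66%) and about 27 at 1.95 (70% to 43%), before any small-sample correction. The plan should state this loss.
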